### Data collection

We will use the existing data collection methods as currently applied by the NICE registry [31]. Most ICUs participating in NICE combine manual entry of data using dedicated software with automated data extractions from electronic patient records available in, *e.g.*, their patient data management system. Each month, participants upload their data from the local, electronic database to the central, electronic registry database. ICUs in the intervention arm that have not submitted their data at the end of a month will be reminded by phone, and assisted if necessary. Quarterly reports are provided within ten weeks after the end of a period, and monthly reports within six weeks. The NICE registry uses a framework for data quality assurance [32], including elements like periodical on-site data quality audits and automated data range and consistency checks. For each ICU, additional data checks for completeness and accuracy will be performed before, during, and after the study period using descriptive statistics.

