### Selection of participants

All 46 ICUs that participate in NICE and (are preparing to) submit data to the registry on the extended quality indicator set will be invited to participate in our study. They should be willing and able to allocate at least two staff members for an average of four hours per month to be involved in the study. The medical manager of the ICU must sign a consent form to formalize the organization's commitment.

All patients admitted to participating ICUs during the study period will be included in the analyses. However, when evaluating the impact on patient outcomes, we will exclude admissions based on the Acute Physiology and Chronic Health Evaluation (APACHE) IV exclusion criteria [26], as well as admissions following cardiac surgery, patients who were dead on admission, and admissions with any of the case mix variables missing.

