### Control arm: basic feedback from the NICE registry

The ICUs allocated to the control arm will be treated as 'regular' NICE participants. This implies they will receive basic quarterly and annual feedback reports on the registry's core outcome indicators case-mix adjusted hospital mortality and length of ICU stay. In addition, they will be sent similar, but separate, basic quarterly and annual feedback reports containing data on the extended indicator set. Also, support by the NICE data managers is available and includes data quality audits, support with data collection, and additional data analyses on request. Furthermore, they are invited to a yearly discussion meeting where they can share experiences with other NICE participants.

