### Strengths and weaknesses of the study design

In our study, we used the previously developed NVIC extended indicator set as the basis for our feedback intervention. Although the NVIC is the national organization representing the Dutch intensive care profession, some ICUs may still disagree with the relevancy of some of the indicators in the set. This would hinder the use of the feedback as input for local QI activities, potentially decreasing the effectiveness of the intervention. However, disagreement with the content of the indicator set was not identified as a barrier in our prospective barriers analysis. We will reassess this during the process evaluation.

Building on an existing indicator set also results in a clear strength of our study, because we are able to use the data collection methods as currently applied by the NICE registry. This will increase the feasibility of the InFoQI program, because eligible ICUs already routinely collect the necessary data items as a result of their participation in NICE; participation in the InFoQI program does not require additional data collection activities. Furthermore, the data quality assurance framework as applied by NICE increases the reliability of the data [31,38], and all recommended data quality control methods for QI projects [39] are being accounted for in our study. This will minimize the probability of missing and erroneous data.

Unfortunately, the design of the study will not allow us to quantitatively evaluate the relative effectiveness of the individual components of the InFoQI program. We considered a factorial design [40] for a separate evaluation of the impact of the comprehensive feedback reports and the outreach visits. However, the strong interconnectedness between the two elements made this difficult. Furthermore, the program aims to successfully overcome known barriers to using performance feedback for improving practice. During the development process of the InFoQI program, it became apparent that in order to achieve this a combination of strategies would be required. Also, previous reviews of the literature reported that multifaceted interventions seem to be more effective than single interventions [15,16,41]. Therefore, we will primarily focus on evaluating the effectiveness of the program as a whole; yet, the process evaluation will provide us with qualitative information on how and to what extent each program element might have contributed to this effectiveness.

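### Only intervention ICUs are actively chased for missed uploads, and admissions with missing case-mix values are dropped, so completeness may differ by arm and could bias the patient outcomes

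*Protocol article*

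**What the plan says.** All outcomes come from the existing registry. Under Data collection, the routine is common to both arms: "Each month, participants upload their data from the local, electronic database to the central, electronic registry database". One element is specific to an arm: "ICUs in the intervention arm that have not submitted their data at the end of a month will be reminded by phone". The same sentence adds help where it is needed. No matching step for control ICUs is stated.

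Control ICUs are not without help. The section on the control arm says that "support by the NICE data managers is available and includes data quality audits, support with data collection, and additional data analyses on request". Data collection also provides that "For each ICU, additional data checks for completeness and accuracy will be performed before, during, and after the study period using descriptive statistics", but it states no action to follow from what those checks show.

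Selection of participants then fixes the analysis set for patient outcomes: "when evaluating the impact on patient outcomes, we will exclude admissions based on the Acute Physiology and Chronic Health Evaluation (APACHE) IV exclusion criteria". The same sentence goes on to remove "patients who were dead on admission, and admissions with any of the case mix variables missing". The rule is limited to patient outcomes.

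The Discussion, under strengths and weaknesses, says of the registry's quality assurance and data quality control: "This will minimize the probability of missing and erroneous data". It does not consider a difference between arms.

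**The concern.** In a cluster trial that takes its outcomes from a registry, the records that exist and are complete at analysis are themselves a consequence of events after randomisation. Here one arm is telephoned and helped when a month's upload is missing, and the other is not. Two further intervention-only elements touch the data: reports that list individual patients, and outreach visits meant in part to raise confidence in the data. All of these could raise completeness in the intervention arm.

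The patient-outcome analysis then conditions on completeness by dropping any admission with a blank case-mix value. If the dropped or unsubmitted admissions differ in length of stay, ventilation time or survival from those kept, and do so to a different extent in the two arms, the comparison is biased. Randomisation does not prevent this, and recruiting more ICUs does not cure it.

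**Working it through.** **1. The plan's own figures.** The article states no missing-data rate, overall or by arm, so there is no figure of this kind to reproduce. The nearest number is the 26 ICUs for length of stay. It cannot be reproduced because no standard deviation is given. It can only be solved backwards, which is done in step 4.

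**2. Two kinds of missingness.**

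| Kind | What triggers it | What differs by arm | Outcomes exposed |
|---|---|---|---|
| Admissions or shifts never submitted | Missed monthly upload | Phone reminder and prompted help, intervention arm only | All, including bed occupancy |
| Submitted admission with a blank case-mix value | Incomplete record | No stated rule differs; patient-level reports and outreach visits could act indirectly | Length of stay, ventilation, mortality |

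The reminder acts directly on the first kind. Its link to the second is plausible but not shown.

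**3. Size of the bias in mean stay.** Let m be the share of an arm's admissions missing from the analysis, and d the mean stay of missing minus included admissions. The full mean of an arm is (1 − m) × included mean + m × missing mean, so the included mean is too low by m × d. The intervention-minus-control difference in means is therefore shifted by

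m(control) × d(control) − m(intervention) × d(intervention),

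which is [m(control) − m(intervention)] × d when d is the same in both arms.

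Neither m nor d is in the article, so both are assumptions. With d between 0.5 and 3 days:

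| Extra share missing, control arm | Shift in days | Relative to the 0.58-day target |
|---|---|---|
| 0 | 0 | 0% |
| 1 point | 0.005 to 0.03 | 1% to 5% |
| 5 points | 0.025 to 0.15 | 4% to 26% |
| 10 points | 0.05 to 0.30 | 9% to 52% |
| 20 points | 0.10 to 0.60 | 17% to 103% |

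One case between these rows: 3% missing against 10%, with d = 2 days, gives (0.10 − 0.03) × 2 = 0.14 days, and 0.14/0.58 = 24%.

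If the missing control stays are the longer ones, the observed reduction is too small. If they are the shorter ones, it is too large. The direction is unknown.

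**4. Is this a matter of power instead?** Inputs from the sample size section: 343 yearly admissions per ICU, intra-cluster correlation 0.036, 26 ICUs (13 per arm), effect 0.58 days, 80% power, 5% error, taken as two-sided.

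- Design effect: 1 + (343 − 1) × 0.036 = 13.312.
- Effective number per arm: 13 × 343 / 13.312 = 335.
- Implied standard deviation: 0.58 / [(1.960 + 0.842) × √(2/335)] = 2.68 days.
- Each control ICU submits 75% of its admissions: effective control number 327, power 79.5%.
- Each submits 50%: effective control number 312, power 78.6%.
- One control ICU lost entirely: power 78.4%. Three lost: 74.3%.

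Thinner data from control ICUs cost little power. The issue is selective missingness.

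**The case against.** The case on the other side is substantial.

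- A reader might infer that control ICUs get no help with data. The article does not support that. They have data-manager support and audits on offer, they upload on the same monthly schedule, and completeness is checked at every ICU. Only the active reminder and the help it prompts are exclusive to one arm.
- A reader might infer that outcome data will in fact be selected differently. That is not established either. A late upload is not a blank severity field. Nothing says that late control data are discarded, and data that arrive before the database closes cause no selection. The reminder probably exists so that the monthly reports, which only intervention ICUs receive, can be produced on time.
- A figure such as 0.14 days rests wholly on assumed inputs and on raw means. The planned analysis is an adjusted competing-risk model for discharge alive, so days do not carry over to its effect estimate. The 0.58-day yardstick also disagrees with the article's own means: 2.11 − 1.28 = 0.83, against which 0.14 is 17%.
- The Discussion's statement on minimising missing data rests on registry procedures that cover both arms, so it is not wrong as such.
- Imputation and sensitivity analyses are commonly left to an analysis plan that is not shown. Their absence from the article is no fault.

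All of this stands, and it limits the point to a possibility of unknown size. It does not remove it. Support on offer is not the same as a call triggered by a missed upload. Checks by descriptive statistics can reveal an imbalance, but no response is stated. The exclusion of admissions with missing case-mix values is a choice that the article itself fixes.

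**Conclusion.** The point holds as a conditional one. As written, the plan contains a route by which allocation can affect the completeness of the outcome and adjustment data, together with a complete-case rule for patient outcomes. Completeness may therefore differ by arm and could bias the comparisons of length of stay, ventilation and mortality. The case-mix exclusion does not reach the bed-occupancy co-primary, which is exposed only if whole periods or shifts are never submitted.

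The size cannot be determined from the article. The bias is zero if missingness is balanced between arms or unrelated to outcome. It could approach the target effect only at the extreme of the assumed range. The figures in days are illustrations. The point deserves action because the remedy is cheap and the bias, if present, could not be repaired by a larger sample.

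**What to change.** 1. Keep the monthly reminder for what the intervention needs, namely timely reports. Separately, apply one identical outcome-data submission and completeness query to both arms, for example at each quarterly close and before database lock. This is the step that deals with unsubmitted admissions and shifts, which imputation cannot recover.
2. In the patient-outcome analyses, replace exclusion for missing case-mix values by multiple imputation that respects clustering by ICU, with the complete-case analysis kept as a sensitivity analysis. The other exclusions can stay as they are.
3. Report completeness by arm: months and shifts submitted, and admissions with any missing case-mix value.

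Cost: some additional calls by existing registry staff, slightly more contact with control ICUs, and some extra analysis work. The control condition of basic feedback reports is unchanged, so the feedback contrast stays intact.

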### Randomization

We will randomly allocate ICUs (clusters) to one of both study arms, stratified by the number of ventilated, non-cardiac surgery admissions (less than the national median versus more than the national median), and involvement in a previous pilot study to evaluate feasibility of data collection of the NVIC indicator set [7] (involved versus not involved). Each stratum will consist of blocks with a randomly assigned size of either two or four ICUs (see Figure 1). A researcher-not involved in the study and blinded to the identity of the units-will use dedicated software to generate a randomization scheme with an equal number of interventions and controls for each block. The size and the randomization scheme of the blocks will be concealed to the investigators enrolling and assigning the ICUs. In an email to the ICU confirming the arm to which they have been allocated, the researcher that executed the randomization process will be sent this information in copy as an additional check on the assignment process. Due to the character of the intervention, it will not be possible to blind participants or the investigators providing the InFoQI program.

**Figure 1 F1:**
[figure not shown]
**Study flow **. * Stratification was based on size (more/less than the national median number of ventilated, non-cardiac surgery admissions) and involvement (yes/no) in a pilot to evaluate feasibility of indicator data collection.

### Statistical analysis

For ICUs in the intervention group, the time from randomization to the first outreach visit-with an expected duration of six to eight weeks-will be regarded as a baseline period. Follow-up will end three months after the last report has been sent, assuming this is the average time required for an ICU to read, discuss, and act on a feedback report. The expected duration for intervention ICUs will therefore be approximately fourteen months. Control ICUs will have a fixed baseline period of two months, and a follow-up of fourteen months.

To assess the effect of the InFoQI program, the outcome values measured during the follow-up period will be compared between both study arms. To assess the effect of the program on length of stay, we will perform a survival analysis of time to alive ICU discharge with dying at the ICU as a competing risk [33], and adjusting for patient demographics, severity of illness during first 24 hours of admission, and admission type. To account for potential correlation of outcomes within ICUs, we will use generalized estimation equations with exchangeable correlation [34-36]. The same procedure will be used to analyze duration of mechanical ventilation. For all-cause mortality, logistic regression analysis will be used, adjusting for severity of illness at ICU admission by using the APACHE IV risk prediction model [26].

To assess the effect of the intervention on the proportion of shifts with a bed occupancy rate above 80%, shift-level occupancy data (0 for an occupancy rate below or equal to 80%, 1 for a rate above 80%) will be analyzed with logistic regression analysis. In this case, generalized estimation equations with an autoregressive correlation structure will be used to account for the longitudinal nature of shift occupancy observations. The same procedure will be followed to analyze the proportion of shifts with a nurse-to-patient ratio below 0.5.

To assess the effect on the proportion of out-of-range glucose measurements, multi-level logistic regression analysis will be performed where subsequent glucose measurements on the same patient are treated as time series data, and both patient-level and ICU-level intercept estimates are used to account for potential correlation of measurements within patients and within ICUs.

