## Methods

### Study design

We will execute a cluster randomized controlled trial to compare facilities participating in the InFoQI program (intervention arm) to facilities receiving basic feedback from the NICE registry (control arm). Because the InFoQI program will be implemented at the facility rather than individual level, a cluster randomized trial is the preferred design for the evaluation of the program's effectiveness [20]. Like most trials aimed at evaluating organizational interventions, our study is pragmatic [21]. To apply to current standards, the study has been designed and will be reported in accordance with the CONSORT statement [22] and the appropriate extensions [23,24].

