### Outcome measures

We used previously collected NICE data (regarding the year 2008) to select outcome measures from the extended quality indicator set to evaluate the effectiveness of our intervention. To decrease the probability of finding positive results by chance as a result of multiple hypothesis testing [28], we limited our primary endpoints to a combination of one patient outcome and one organizational process measure. We selected the indicators that showed the largest room for improvement, *i.e.*, the largest difference between the average of top-performing centers and the average of the remaining centers [29].

Primary outcome measures will be:

1. Length of ICU stay (ICU LOS); this will be calculated as the difference in days between the time of ICU discharge and time of ICU admission. To account for patients being discharged too early, the length of stay of the first ICU admission will be prolonged with the length of stay of subsequent ICU readmissions within the same hospital admission.

2. Proportion of shifts with a bed occupancy rate above 80%; this threshold is set by the NVIC in their national organizational guideline for ICUs [30]. We will calculate the bed occupancy rate as the maximum number of patients admitted simultaneously during an eight-hour nursing shift divided by the number of operational beds in that same shift. A bed will be defined as 'operational' when it is fitted with monitoring and ventilation equipment and scheduled nursing staff.

Secondary outcome measures will be all-cause, in-hospital mortality of ICU patients, duration of mechanical ventilation, proportion of glucose measurements outside the range of 2.2 to 8.0 mmol/L, and the proportion of shifts with a nurse-to-patient ratio below 0.5.

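### The mortality model is the only one not explicitly tied to a method for within-ICU correlation; read literally, its interval and p-value would be too optimistic

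*Protocol article*

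**What the plan says.** The ICU is the unit of allocation. Study design states "We will execute a cluster randomized controlled trial", and Randomization states "We will randomly allocate ICUs (clusters) to one of both study arms". Mortality is listed first among the secondary outcomes: "Secondary outcome measures will be all-cause, in-hospital mortality of ICU patients".

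The Statistical analysis section then takes the outcomes in turn:

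- **Length of ICU stay:** a competing-risk survival model with case-mix adjustment, followed by "To account for potential correlation of outcomes within ICUs, we will use generalized estimation equations with exchangeable correlation".
- **Mechanical ventilation:** "The same procedure will be used to analyze duration of mechanical ventilation".
- **Mortality:** "For all-cause mortality, logistic regression analysis will be used, adjusting for severity of illness at ICU admission", by means of APACHE IV. The sentence names no correlation method.
- **Bed occupancy:** logistic regression, followed by "In this case, generalized estimation equations with an autoregressive correlation structure will be used". The nurse-to-patient ratio is to be handled in the same way.
- **Glucose:** multi-level logistic regression in which "both patient-level and ICU-level intercept estimates are used to account for potential correlation".

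**The concern.** Mortality is the one outcome for which a reader cannot point to a stated cluster method or to an explicit link to one. APACHE IV adjustment does not fill the gap. It removes differences in patient risk, but ICUs can still differ in mortality after case-mix adjustment, and that remaining variation correlates outcomes within an ICU. The protocol accepts this logic for length of stay, where it plans GEE in addition to severity adjustment.

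Two analysts could follow the same text and report materially different intervals. Under the literal reading, some 10,400 patients (26 × 400) would be treated as independent when about 26 units were randomised. A chance difference between ICUs could then appear as a nominally significant benefit or harm on mortality, reported beside an intervention intended to shorten ICU stay.

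**Working it through.** **Inputs from the protocol article**

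- 343 admissions per ICU per year, and at least 26 ICUs completing (Sample size calculations).
- Follow-up of fourteen months (Statistical analysis).
- Type I error 5% (Sample size calculations). Sidedness is not stated; two-sided is used here.
- Intra-cluster correlation (ICC) of 0.036 for length of stay and 0.278 for occupancy (Sample size calculations). None is given for mortality.

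**Assumption.** The residual mortality ICC after APACHE IV adjustment is taken as 0.001 to 0.01.

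**The plan's own figure.** There is none for mortality to reproduce. The nearest is 26 ICUs for length of stay. Its design effect is 1 + (343 − 1) × 0.036 = 13.31, but the standard deviation of length of stay is not stated, so the 26 can be neither confirmed nor refuted. It serves here only as the number of clusters.

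**Step 1, cluster size.** m = 343 × 14/12 ≈ 400.

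**Step 2, cost of ignoring clustering.** Design effect DE = 1 + (m − 1) × ICC. The standard error is too small by a factor √DE. The true type I error of a nominal 5% test is 2 × (1 − Φ(1.96/√DE)). For ICC 0.005: DE = 1 + 399 × 0.005 = 3.00, √DE = 1.73, 1.96/1.73 = 1.13, type I error 25.7%.

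| Assumed ICC | DE (m = 400) | SE too small by | True type I error | Same, m = 343 |
|---|---|---|---|---|
| 0.001 | 1.40 | 1.18 | 9.8% | 9.1% |
| 0.002 | 1.80 | 1.34 | 14.4% | 13.1% |
| 0.005 | 3.00 | 1.73 | 25.7% | 23.4% |
| 0.01 | 4.99 | 2.23 | 38.0% | 35.1% |

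Because the clusters are large, even a very small ICC matters, and the result depends little on which cluster size is used.

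**Step 3, simulation check.** Beta-binomial data were simulated with 26 ICUs of 400 patients, an assumed mortality of 15%, no covariates and 4,000 runs.

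| Assumed ICC | Rejects, clustering ignored | Rejects, cluster-robust variance |
|---|---|---|
| 0 | 5.3% | 7.3% |
| 0.001 | 9.6% | 7.2% |
| 0.005 | 25.8% | 7.7% |
| 0.01 | 38.8% | 7.4% |

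The first column agrees with the formula. The second shows that an uncorrected sandwich variance with 26 clusters removes most of the inflation but still rejects in about 7% to 8% of runs. That is the reason for asking for a small-sample correction.

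**The case against.** The strongest reply is that the text already covers mortality. The sentence "To account for potential correlation of outcomes within ICUs, we will use generalized estimation equations with exchangeable correlation" speaks of outcomes in general, is not limited to length of stay, and stands in the same paragraph as the mortality model. The next paragraph marks a change of structure for the shift outcomes, which reads naturally if exchangeable GEE is the default for all patient-level outcomes before it. The occupancy text also uses logistic regression as the name of the mean model and states the correlation handling separately, so that label alone does not imply independence. The authors justify the cluster design, use ICCs in the sample size, and commit to CONSORT and its relevant extensions. A full protocol or analysis plan that is not shown may settle the matter.

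Much of this stands. A reader might infer that the trial has decided to analyse mortality without any cluster term, so that its interval will be too narrow. The article does not say so, and elliptical drafting is a plausible explanation. A reader might also treat mortality as the trial's designated safety check. The article gives it no such role and does not expect to detect an effect on it.

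The reply does not remove the ambiguity. The GEE sentence directly follows the length-of-stay model, the procedure is then extended by name to ventilation, and mortality is given a different model. The other two logistic analyses each have their correlation method beside them. Nor is this a point simply deferred to another document: the article fixes the model and the adjustment for mortality, and the missing link stands out against its own treatment of every other outcome. Low power offers no protection, since under the literal reading a nominally significant mortality result is more likely to be an artefact.

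**Conclusion.** The point holds in conditional form. The mortality model is not explicitly linked to a method for within-ICU correlation, and the surrounding text permits either reading. If exchangeable GEE was meant to apply, the defect is one of wording. If the sentence is followed literally, the standard error is too small by a factor of about 1.2 to 2.2, and a nominal 5% test rejects about 10% to 38% of the time under no effect.

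That range rests on about 400 admissions per ICU, a two-sided test, and an assumed residual ICC of 0.001 to 0.01. Since APACHE IV adjustment should lower the ICC, the lower end deserves as much weight as the upper. The consequence is confined to one secondary outcome.

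**What to change.** Add one sentence to the mortality analysis. It should state that the logistic regression uses GEE with exchangeable correlation by ICU, with a small-sample correction for about 26 clusters, or alternatively an ICU random intercept. Keep the APACHE IV adjustment and include the two stratification factors used at randomisation (ICU size and involvement in the pilot).

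The cost is that sentence and, compared with the literal reading, an appropriately wider mortality interval. No change to design, sample size or data collection is needed. If exchangeable GEE was always intended, the sentence merely records it and adds the small-sample correction and the strata.
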